#### **4.9.3 Poisson regression**

We will conduct a sensitivity analysis of the primary endpoint using Poisson regression i.e. using a generalised linear mixed model assuming a Poisson distribution and a Log link. The dependent variable will be a binary indicator (yes vs no) indicating whether the primary outcome occurred for each subject. Covariates will include the randomised group and prior use of insulin as fixed effects and a random effect of study site. The model will adjust for exposure (in years) defined as time to event or censoring, using the same definition as the one used for the survival analysis. The Poisson model will be used to estimate the yearly event rate and 95% confidence interval in each group. The effect of the intervention will be estimated as the rate ratio and its 95% confidence interval. SAS GLIMMIX procedure will be used.

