### **3.6 STATISTICAL METHODS**

Analysis will be based on the principle of intention-to-treat. The effectiveness of the study intervention on the primary outcomes will be determined using Cox models for survival data, with censoring of participants who develop a subsequent pregnancy during follow-up. Given that the occurrence of primary outcomes can only be registered to the date of ascertainment during study visits, the use of other methods (e.g. Poisson regression) for the primary analysis will be explored during the blind review and will be finalised in the Statistical Analysis Plan prior to database lock and unblinding. Analyses of secondary outcomes will be conducted using standard statistical procedures applicable to dichotomous, categorical or continuous data as appropriate.

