#### **5.1.4 Six month visits (Month 6, 12, 18, 24, 30, and 36)**

1. Measure weight, waist circumference, and blood pressure.
2. Determine whether an interim diagnosis of T2DM has been made.
3. If an interim diagnosis of T2DM has been made, obtain confirmatory source documentation. The participants will not be followed up further, and will be discontinued from the study intervention. Data will be censored for these participants.
4. At Months 6, 18, and 30, perform HbA1c. If value is more than 6.5%, then call patient for OGTT.
5. At Months 12, 24 and 36, perform OGTT, unless an interim diagnosis of T2DM has been made, and source documentation is available. Participants who change glycaemic category, but do not develop T2DM, will be followed up.
6. Administer diet and physical activity questionnaires.
7. Record healthcare utilisation since the last study visit.
8. Record any serious adverse events since the last study visit.

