## 2.6 Sample Size

A sample size of 1414 women with GDM will provide 90% power ( $2\alpha=0.05$ ) to detect a relative risk of 0.65, assuming that the control group cumulative incidence for change in glycaemic category will be 20% at 24 months and allowing for 20% of missing outcome data.

The initial power calculation was based on a chi-square test comparing two proportions at 24 months; however, to account for various study durations, the primary analysis will consist in a survival analysis of time to change in glycaemic category which is expected to have at least the same power as a comparison of proportions.

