### 4.1 General Principles

Analyses will be performed using SAS Enterprise Guide version 8.3 or higher (SAS Institute Inc., Cary, NC, USA).

All variables will be analysed by descriptive statistical methods. The number of data available and missing data, mean, standard deviation, minimum, quartiles, median, and maximum will be calculated for continuous data. Frequency tables will be generated for categorical data. For categorical variables, the number and percentage of patients with a specific level of the variable will be presented.

All tests will be two-sided with a type-I error rate of 5%. Analyses of the primary outcome (change in category of glycaemia from normoglycaemia to IGT, IFG or T2DM or from IFG or IGT to T2DM) will be unadjusted for multiplicity; however, we will control the family-wise error rate across secondary outcomes using a Holm-Bonferroni correction [2]. No other multiplicity adjustment will be applied.

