#### 4.10 Secondary outcomes

Secondary outcomes include the following variables:

- Development of T2DM
- Fasting blood glucose
- Body weight
- Waist circumference
- Systolic blood pressure
- Physical activity level defined as the average daily MET (see definition in Section 3.7)
- Diet defined as the total 24-hour calorie intake (see definition in Section 3.8)

Development of T2DM will be analysed in the same way as the primary outcome, i.e. using survival analysis and Poisson regression as described in sections 4.9.2 and 4.9.3. No adjusted or subgroup analyses will be applied to this outcome except for a subgroup analysis according to baseline glycaemic status (normoglycaemia vs pre-diabetes).

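### The Poisson sensitivity analysis in SAP 4.9.3 ignores that events are dated only at OGTT visits: on the documented calendar its standard error is about 4-7% too large and its control yearly rate about 5-6% too low

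*Combined protocol and SAP*

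**What the plan says.** Protocol 3.6 plans Cox models but notes that "the occurrence of primary outcomes can only be registered to the date of ascertainment during study visits". It offers Poisson regression as an example of another method to be explored for that reason.

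SAP 4.9.2 makes the Cox model primary. Women without an event are censored at their last OGTT. SAP 4.9.3 then adds a sensitivity analysis "using a generalised linear mixed model assuming a Poisson distribution and a Log link", and states: "The dependent variable will be a binary indicator (yes vs no) indicating whether the primary outcome occurred for each subject". Exposure is time to event or censoring in years, defined as for the survival analysis. Insulin use is a fixed effect and site a random effect. The output is a yearly event rate per arm and a rate ratio, each with a 95% confidence interval. GLIMMIX is named; no robust variance or scale parameter is mentioned.

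The OGTT schedule is in protocol 5.1.4: "At Months 12, 24 and 36, perform OGTT". At months 6, 18 and 30 only HbA1c is measured, and a raised value triggers an OGTT. A further OGTT falls at the end-of-study (EOS) visit. Under Table 3, visits during lockdown (from 25 March 2020) were remote and without OGTT.

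SAP 4.10 analyses development of T2DM in the same way, "using survival analysis and Poisson regression as described in sections 4.9.2 and 4.9.3".

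**The concern.** A Poisson likelihood with a person-time offset reproduces the exponential survival likelihood when each event time is known. Here a woman who worsens in month 3 is recorded at month 12. This has two consequences.

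- **Variance.** Within an OGTT interval the outcome is Bernoulli, with variance q(1-q), where q is the chance of an event in that interval. The Poisson model uses q, so a model-based standard error is too large.
- **Exposure.** Women with events contribute event-free time up to detection. The yearly rate is therefore too low, more so in the arm with the higher hazard, which moves the rate ratio away from the underlying hazard ratio and towards 1.

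At stake are the planned check on the primary result, the second analysis of T2DM, and the only absolute yearly rates in the plan. There is also a question of purpose: the model uses the same dates as the Cox model, so it cannot test whether those dates matter.

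**Working it through.** **Inputs.** From SAP 2.6: control incidence 20% at 24 months, relative risk 0.65 (so 13% with intervention), 20% missing outcomes, 1414 women. From SAP 2.2: minimum follow-up 12 months, EOS visits July 2020 to January 2021. From protocol 3.5: median follow-up 24 months. The 27% in protocol 3.5 is a T2DM figure at 20 months; using it as a 24-month incidence of the primary outcome is an assumption, made to give an upper value.

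**1. The plan's own figure.** A two-proportion test of 20% against 13%, two-sided 5%, 90% power, needs 589 per arm, 1178 in total. 1178 × 1.2 = 1413.6, which gives the stated 1414. The inputs are therefore read as the SAP meant them. The SAP gives no figure for the Poisson analysis itself.

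**2. Underlying hazards (constant hazard assumed).** Control: -ln(0.80)/2 = 0.1116 per year. Intervention: -ln(0.87)/2 = 0.0696. Hazard ratio: ln(0.87)/ln(0.80) = 0.624.

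**3. What the Poisson model estimates with yearly OGTTs.** Event probability per year: q0 = 1 - exp(-0.1116) = 0.1056 and q1 = 1 - exp(-0.0696) = 0.0673. Each interval is credited as a full year, so these are the fitted rates.
- Rate ratio: q1/q0 = 0.637 against 0.624.
- Control yearly rate: 0.1056 against 0.1116, which is 5.4% low.

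**4. Standard error.** Per interval, the Poisson variance of the log ratio is proportional to 1/q0 + 1/q1, and the true variance to (1-q0)/q0 + (1-q1)/q1, which is 2 less.
- Yearly OGTT, 20%: 24.34/22.34 = 1.0895, square root 1.044.
- Yearly OGTT, 27% (q0 = 0.1456, q1 = 0.0920): 17.74/15.74 = 1.127, square root 1.062.

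**5. Type I error.** With no effect and yearly OGTTs, the ratio is 1/√(1 - 0.1056) = 1.057. The effective critical value is 1.96 × 1.057 = 2.07, which gives 3.8%. Simulation gave 3.8-3.9% with model-based errors and 4.8% with robust errors.

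**6. Control case.** With exact event dates, simulation gave a model-to-robust ratio of 1.00 and no bias in the ratio or the rates. Visit dating is the whole cause.

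**7. The documented calendar.** Trials were simulated with EOS spread over July 2020 to January 2021, yearly OGTTs only before 25 March 2020, and follow-up of 12-36 months. About 28% of women then have their only OGTT at EOS. At 20% incidence the standard error is about 4-7% too large, type I error about 3.5-4%, the ratio about 0.635 and the control rate about 5-6% low. At 27% the standard error is up to about 8% too large.

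**8. What moves the figures.**

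| Situation | Standard error too large by |
|---|---|
| Every event caught at six-monthly visits, 20% | about 2% |
| Hazard 2-3 times higher in year 1, 20% | 2-3% |
| 30% of events caught by HbA1c-triggered OGTT, 20% | 3.4% |
| One OGTT per woman, at 24 months, 20% | 9.0% |
| One OGTT per woman, at 24 months, 27% | 12.7% |

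**9. Power.** In a 600-trial comparison on the yearly schedule, the planned model had 87.0% and the complementary log-log model 88.2%.

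The simulations left out the site and insulin terms.

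**The case against.** The strongest reply is that this is a small, conservative error in a sensitivity analysis. Type I error stays below 5%, so it cannot manufacture a positive finding, and SAP Table 8 marks the Cox model as primary. That stands, and it limits the weight of the point.

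Several stronger readings are tempting, and the documents do not support them.

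- **That a yes/no outcome should not go into a Poisson model.** With a person-time offset this is the exponential survival likelihood, and with exact dates its errors are right (step 6).
- **That intervals are 9-13% too wide because of lockdown.** That requires most women to have had a single OGTT. A woman with 24 or more months of follow-up at an EOS visit no later than January 2021 reached month 12 by the end of January 2020, before lockdown. Lockdown could remove the month-12 OGTT only for women with less than about 22 months of follow-up. Widespread missed visits for other reasons could raise the figure, but the documents give no rate for them.
- **That the ratio is pulled towards 1 relative to the design effect.** The shift is against the underlying hazard ratio of 0.624, which follows from the SAP's figures under constant hazard. Against the design relative risk of 0.65, a value of 0.635 is not nearer 1.
- **That the SAP prescribes model-based errors.** It is silent; they are inferred because it names GLIMMIX and no other estimator.

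It can also be said that SAP 4.9.6 repeats the model with HbA1c and fasting glucose where a scheduled OGTT was not done. This fills some gaps but leaves the dating at visits unmodelled.

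**Conclusion.** The point holds as a modest one. On the documented calendar and at 20% control incidence, the planned Poisson analysis has a standard error about 4-7% too large, type I error of about 3.5-4%, a ratio of about 0.635 against 0.624, and a control yearly rate about 5-6% too low. The cost is about one point of power. These figures assume constant hazard, model-based errors, follow-up of 12-36 months, and events dated at OGTTs. Interim T2DM diagnoses dated between visits, or a front-loaded hazard, would make them smaller.

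The more important weakness is one of purpose. Protocol 3.6 raised Poisson regression because of visit-dated ascertainment, and SAP 4.9.3 reuses the Cox dates without modelling the interval. If the two analyses agree, that says nothing about whether visit dating matters.

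**What to change.** In SAP 4.9.3, and for T2DM in 4.10, keep GLIMMIX, the covariates and the site random effect, and change the rest:

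- one row per woman per OGTT interval, ending at the interval in which the change is detected or at the last OGTT;
- binomial distribution with a complementary log-log link;
- log of the interval length in years as offset;
- report the exponentiated group coefficient as a hazard ratio, and the yearly hazard per arm in place of the Poisson rate.

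In simulation this model gave a ratio of 0.62, a standard error within 2% of the true value (ratio 0.98-1.02), and type I error of 4.3-5.1%. Adding robust errors to the Poisson model would repair the interval width but not the ratio or the rates. The analyses that refer back to 4.9.3 (4.9.4, 4.9.5 and 4.9.6) would follow; in 4.9.6 the intervals would run between visits with any usable glycaemic measure.

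Cost: one rewritten SAP paragraph and a long-format dataset. No new data are needed.

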#### **4.9.4 Adjusted analyses**

Both the Cox and Poisson models will be repeated after adding the following covariates to the model: prediabetes (yes/on), BMI (underweight, normal, overweight, obese), time since GDM-affected pregnancy (as a continuous variable, measured in months) and age (as a continuous variable, measured in years).

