#### 5.1.2 Registration visit (3-18 months post-partum)

1. Perform OGTT and measure HbA1c.
2. If OGTT indicates T2DM, refer for care; if OGTT does not indicate T2DM, invite patient to participate in trial, and arrange randomisation visit appointment (could be same day).

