## 4.9 Analysis of the primary outcome

The primary outcome is a change of glycaemic category, at or prior to final visit defined as:

- A change from Normal glucose tolerance (NGT) to impaired fasting glucose (IFG) or impaired glucose tolerance (IGT), or T2DM
- A change from IFG or IGT to T2DM

This will be diagnosed using ADA criteria as given below:

- Normal glucose tolerance (<100 mg/dL fasting and <140 mg/dL post-glucose load)
- Impaired glucose tolerance (<100 mg/dL fasting and 140-199 mg/dL post-load)
- Impaired fasting glucose (100-125 mg/dL fasting and <140mg/dL post-load)
- Type 2 diabetes ( $\geq 126$  mg/dL fasting or  $\geq 200$  mg/dL post-load)

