### 4.9.2 Survival analysis

Change in glycaemic category for primary outcome as defined in section 2.4.1 will be analysed as a time to event calculated as the number of days between randomisation and the day of the event. For subjects with no event, data will be censored on the day of the last OGTT test results.

Survival by treatment arm will be described using a Kaplan-Meier plot with 95% confidence interval will be reported by treatment arm. If available, median time to event as well as quartiles will be derived from the Kaplan-Meier estimates. Censoring will be done at time of last OGTT test.

A Cox model will be used to estimate the Hazard ratio of the two arms (Intervention compared to Control). The Cox model will include the randomised group as well as prior use of insulin as fixed effects and study site as a random effect [4]. We will visually assess the proportional hazard assumption. SAS Proc PHREG will be used.

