| Time Since Delivery
N
mean (SD)
Q1 Q2 Q3
Min, Max     |  |  |  |
| Family History of Diabetes
Yes
No                           |  |  |  |
| Family History of Hypertension
Yes
No                       |  |  |  |
| Past History of Gestational Diabetes
Yes
No                 |  |  |  |
| Use of Insulin in Index Pregnancy
Yes
No                    |  |  |  |
| Past Use of Insulin
Yes
No                                  |  |  |  |
| Past Use of Medication
Yes
No                               |  |  |  |
| Alcohol Consumption
Yes
No                                  |  |  |  |
| Tobacco Use
Yes
No                                          |  |  |  |
| Height
N                                                       |  |  |  |

|                                                                                                              |  |  |  |
|--------------------------------------------------------------------------------------------------------------|--|--|--|
| mean (SD)
Q1 Q2 Q3
Min, Max                                                                            |  |  |  |
| Weight
N
mean (SD)
Q1 Q2 Q3
Min, Max                                                      |  |  |  |
| BMI
Underweight
Normal
Overweight
Obese                                                   |  |  |  |
| HbA1c (%)
N
mean (SD)
Q1 Q2 Q3
Min, Max                                                   |  |  |  |
| Glucose 0 min (mmol/L) at
baseline postpartum (mg/dl)
N
mean (SD)
Q1 Q2 Q3
Min, Max   |  |  |  |
| Glucose 120 min (mmol/L) at
baseline postpartum (mg/dl)
N
mean (SD)
Q1 Q2 Q3
Min, Max |  |  |  |
| Waist Circumference
N
mean (SD)
Q1 Q2 Q3
Min, Max                                         |  |  |  |
| WC(>80cm)
Yes
No                                                                             |  |  |  |
| Hip Circumference
N
mean (SD)
Q1 Q2 Q3
Min, Max                                           |  |  |  |
| Waist/Hip Ratio
N
mean (SD)
Q1 Q2 Q3
Min, Max                                             |  |  |  |
| Hypertension
Yes
No                                                                             |  |  |  |

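### The supportive adjusted models in SAP 4.9.4 use baseline glycaemia only as prediabetes yes/no and leave out the measured fasting and 2-hour glucose, on which the risk of crossing the outcome cut-off depends

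*Combined protocol and SAP*

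**What the plan says.** - **Adjusted models.** SAP 4.9.4 repeats the Cox and Poisson models after "adding the following covariates to the model: prediabetes (yes/on), BMI (underweight, normal, overweight, obese"). The printed yes/on is an evident slip for yes/no. Age and time since the GDM pregnancy follow as continuous variables. No glucose value is included.
- **Primary model.** The Cox model in SAP 4.9.2 contains the "randomised group as well as prior use of insulin as fixed effects and study site as a random effect". The footnote to SAP Table 8 marks this survival row as the primary analysis. The adjusted row is printed directly beneath it.
- **Event.** SAP 4.9 defines normal status as "Normal glucose tolerance (<100 mg/dL fasting and <140 mg/dL post-glucose load"), and a woman normal at baseline has an event when she leaves that category. For women with IFG or IGT the event is "A change from IFG or IGT to T2DM", that is, fasting of at least 126 or 2-hour of at least 200 mg/dL.
- **Available data.** Protocol 5.1.2 requires staff to "Perform OGTT and measure HbA1c" at registration, and that OGTT decides eligibility. SAP Table 3 summarises the fasting value and the 2-hour value ("Glucose 120 min (mmol/L")) as continuous variables.
- **Practice elsewhere in the SAP.** Section 4.10.2 adjusts every continuous secondary outcome, fasting glucose included, for its continuous baseline value.
- **Balance by design.** Randomisation is stratified by country, centre and insulin use (SAP 2.5), not by glycaemic status or glucose.

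**The concern.** The flag tells the model which cut-off applies to a woman, and nothing about how close she is to it. A woman with fasting 98 and 2-hour 135 mg/dL and one with 78 and 90 are both coded as not having prediabetes. The first is 2 and 5 mg/dL from an event, the second 22 and 50. The same holds among women with prediabetes relative to 126/200.

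Two things follow for the adjusted analysis. Chance imbalance between arms in closeness to the cut-off stays in the estimate, and nothing in the stratification prevents it. A strong predictor is also omitted from a hazard model, which pulls the hazard ratio towards 1 and weakens the test. Readers will use the adjusted row of Table 8 to judge whether the primary result survives adjustment for baseline. As written, it cannot answer that for the variable that defines the event.

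**Working it through.** **1. The plan's own figure.** The documents state no efficiency for the adjusted analysis, so the only figure to reproduce is the design. With 20% versus 13% (relative risk 0.65), two-sided 5% and 90% power, the normal-approximation formula for two proportions gives 588.8, so 589 per arm and 1178 in total. Then 1178 × 1.2 = 1413.6, rounded up to 1414, which matches SAP 2.6. With 20% missing, 1414 × 0.8 = 1131 women are evaluable. Power is then 88.8%, and expected events are 1131 × (0.20 + 0.13)/2 = about 187.

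**2. Measure of loss.** Let z = log HR / SE for the treatment term. Then loss = 1 − z²(flag only) / z²(flag plus continuous glucose).

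**3. Threshold-crossing simulations.** Every glucose input here is an assumption. OGTTs fall at months 12 and 24, and control and treated risks were calibrated to 20% and 13%. Each scenario has 300,000 simulated women, so the losses reflect expected values rather than the noise of one trial. Correlation between fasting and 2-hour values is 0.5. Drift is the between-woman SD of change, in SD units per year.

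| Scenario: mean fasting / 2-hour (SD 9 / 28); within-person SD fasting / 2-hour | Drift | Cox loss | Poisson loss | Variance of log HR, Cox, full ÷ flag |
|---|---|---|---|---|
| 90 / 120; 5 / 15 (central) | 0.2 | 10.2% | 9.5% | 1.0011 |
| same | 0.8 | 5.1% | 4.7% | 1.0005 |
| 90 / 120; 3 / 8 | 0.2 | 19.7% | 15.9% | 1.0026 |
| same | 0.8 | 6.5% | 5.5% | 1.0007 |
| 90 / 120; 7 / 25 | 0.2 | 4.7% | 5.2% | 1.0004 |
| same | 0.8 | 3.2% | 3.2% | 1.0003 |
| 96 / 135; 5 / 15 | 0.2 | 9.0% | 8.5% | 1.0014 |
| same | 0.8 | 4.0% | 3.8% | 1.0005 |

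**4. Where the loss comes from.** In a separate run of the 96/135, low-drift scenario (57% with prediabetes), the Cox log HR moved from −0.467 to −0.486 when glucose was added, and the scaled SE from 5.040 to 5.042. So z² ratio = (0.467/0.486)² × (5.042/5.040)² = 0.924, a loss of 7.6%; the run in the table gave 9.0%. The estimate moves (HR 0.627 to 0.615) and the SE does not. The interval on the log scale keeps its width.

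**5. Constant-hazard-ratio model.** Here glucose acts through a fixed hazard ratio per SD within status group.

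| HR per SD | 1.35 | 1.65 | 2.23 | 2.72 | 3.67 |
|---|---|---|---|---|---|
| Loss | 0.3% | 1.9% | 9.2% | 10.8% | 15.7% |

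If glucose is only weakly prognostic within status group, almost nothing is lost.

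**6. Other assumed distributions.** Separate simulations gave gains in squared test statistic from 3% to 25%. Since loss = 1 − 1/(1 + gain), that is a loss of 2.9% to 20%. One of these sets, with 24% and 60% prediabetes, gave gains of 3-12% (loss 2.9-10.7%) with the SE ratio at 1.00.

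**7. Chance imbalance.** With assumed means of 88 and 112 mg/dL, flag-adjusted and distance-adjusted log HRs in the same trial differed with an SD of 0.04 to 0.08, against an SE of 0.12 to 0.16. About 6-12% of those runs did not converge and were left out. At HR 0.65, a difference of 0.06 corresponds to 0.65 × exp(±0.06) = 0.61 to 0.69.

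**8. Scale in power terms, as illustration only.** Suppose the flag-adjusted test had the design power of 88.8%, so expected z = 1.960 + 1.216 = 3.176. Dividing by √0.95, √0.90 or √0.80 gives 3.258, 3.348 or 3.551, that is, power of 90.3%, 91.7% or 94.4%.

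**The case against.** - **No decision rests on 4.9.4.** This stands. The primary row in Table 8 is the model with group, insulin and site. The 90% in SAP 2.6 belongs to the primary comparison, and the documents claim no power for the adjusted repeat.
- **The larger effect is mostly a different estimand.** This also stands. Hazard ratios are non-collapsible, so adding a prognostic covariate in a randomised trial moves the conditional HR away from 1 without any bias having been present. A reader might infer that adjustment would tighten the interval, or that the plan discards a fixed share of its information. Neither is supported: the variance is unchanged, and only the test statistic gains.
- **The size cannot be derived from the documents.** This stands. The nearest figure is the pilot in Protocol 2.1, with 40% IFG/IGT and 28% normal, or 40/68 = 59% prediabetes among women without diabetes. It describes women screened at a mean of 20 months after delivery and gives no glucose means or SDs.
- **The comparator is simplified.** The simulations in working steps 3 to 5 compare arm plus flag with arm plus flag plus glucose. The SAP model also holds BMI, age, time since pregnancy, insulin and site, and some of these may carry part of the same risk. The gain over the full SAP model could be smaller.
- **A clinical category is a legitimate covariate.** It is, and the adjusted analysis is valid as written. The category identifies which event applies and matches the subgroup variable in SAP 4.9.5. That is a reason to keep the flag. It does not justify leaving out measured values that the SAP would use for a continuous outcome.

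**Conclusion.** The concern holds as a limited improvement to a supportive analysis. The adjusted Cox and Poisson models omit the two measurements that define the event, although the plan collects both and follows the opposite practice for its continuous secondary outcomes. The cost is some test efficiency, roughly 0-20% of the squared test statistic and typically about 5-10%, together with uncorrected chance imbalance in distance to the cut-off. These figures rest on assumed glucose distributions, within-person variability and drift, and should be quoted only as a range under assumption.

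A reader might go further and conclude that the primary result is biased or underpowered. The documents do not support that: the primary Cox model has no glycaemia term, is valid under randomisation, and keeps its stated power whatever is done in 4.9.4.

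**What to change.** In SAP 4.9.4, before database lock and unblinding:

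1. Keep the prediabetes flag, because it determines which event counts.
2. Add baseline fasting and 2-hour glucose as continuous covariates, each with its interaction with the flag. If few women with prediabetes have events, use instead each woman's distance to the fasting and 2-hour cut-offs that apply to her, which needs fewer terms and is more stable. State in advance the rule for choosing between the two.
3. Use the same set in the Cox and Poisson adjusted models, and leave the other covariates as they are.
4. State that the adjusted hazard ratio is conditional on more covariates than the primary one, so that a difference between the two rows of Table 8 is not read as bias in either.

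Cost: SAP wording and up to four more degrees of freedom, against about 187 expected events at the design point. No new data are needed. The price in interpretation is a hazard ratio less directly comparable with the primary one, which item 4 addresses. If the database has already been unblinded, the change should be labelled post hoc.
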